### Trial assessments

Schedule of assessments and visits is summarised in Fig. 1 according to the SPIRIT statement [22, 23].

**Fig. 1 Fig1:**
[figure not shown]
Trial assessments. ^1^Only weight at the end of study visit. ^2^The required screening blood tests are urea, electrolytes, calcium, HIV, hepatitis B, hepatitis C, syphilis, pneumococcal and varicella serology. ^3^Full blood count, liver function tests and immunoglobulins. ^4^Only at month 6, 12 and end of trial visit. IVIG intravenous immunoglobulin, PANSS Positive and Negative Syndrome Scale

### Anti-neuronal membrane antibody assays

We use a live cell-based assay system [24] to identify serum anti-neuronal membrane antibodies. We have identified criteria to attempt to distinguish clinically irrelevant cases of positive anti-NMDAR and VGKC complex antibodies from pathogenic antibodies [12, 25].

Anti-neuronal membrane antibody assays will be performed for NMDAR, LGI1 and GABA-A antibodies. During the course of the study, other relevant anti-neuronal antibodies may be discovered and the protocol allows for these to be included, as determined by the Trial Steering Committee. Anti-neuronal membrane antibodies will be assessed at screening, the first rituximab treatment visit (28–35 days), at 6 and 12-month follow-up, and at the end of study clinical visit.

### Safety monitoring

The screening blood tests will be performed only at the screening visit and will include urea, electrolytes, calcium, HIV, hepatitis B, hepatitis C, syphilis, pneumococcal and varicella serology.

The monitoring blood samples will be taken at the screening visit, at 6 and 12-month follow-up visits and at the end of study clinical visit. Monitoring blood tests include FBC, liver function tests (LFT) and immunoglobulin levels.

Pregnancy is an exclusion factor. A pregnancy test (urine sample) will be conducted with female participants at the screening visit to confirm the eligibility of a potential trial participant. A further pregnancy test will be performed at the baseline visit (no longer than 7 days before the first dose of IVIG). Another and final pregnancy test should be taken no longer than 7 days before the first dose of rituximab.

The trial participants’ or their partners’ pregnancies during the trial period and up to 2 years after trial enrolment will be reported using the relevant Pregnancy Reporting Forms within 24 h of notification.

### Primary outcome measure

The Positive and Negative Syndrome Scale (PANSS) [18] is a clinician/researcher-rated 30-item scale for the assessment of the severity of symptoms of schizophrenia based on information obtained from a patient during the interview and from their family members and clinicians. Each item is rated from 1 (absent) to 7 (extreme) and they are grouped into three subscales: Positive Scale, P (7 items); Negative Scale, N (7 items); and General Psychopathology Scale, G (16 items). The sum of individual ratings within each subscale gives score ranges of 7–49 for the Positive Scale and Negative Scale and of 16–112 for the General Pathology Scale. A higher score indicates severe symptoms.

The primary outcome will be assessed by eight selected PANSS items [21]. These include three Positive Scale items (P1, delusions; P2, conceptual disorganisation; P3, hallucinatory behaviour), three Negative Scale items (N1, blunted affect; N4, passive/apathetic social withdrawal; N6, lack of spontaneity) and two items from the General Pathology Scale (G5, mannerisms/posturing; G9, unusual thought content).

PANSS assessments will be conducted by trained researchers. Their training includes PANSS training by certified trainers followed by observed role-play interviews with feedback, observed mock interviews with non-patients and patients with psychosis, and mock-interview videoing and analysis. Thereafter, there will be periodical refresher training with certified PANSS trainers and researchers’ independent rating of individual patient video interviews over the trial period.

### Trial procedures

#### Identification of potential participants and enrolment

Participants will be identified to a SINAPPS2 trial neurologist either by referral from their mental health care team after receiving positive results for their routine antibody testing in clinical practice or after having been tested within the screening study on the prevalence of antibody-associated psychosis (PPiP2 study, REC ref: 12/EE/0307). The trial flow is summarised in Fig. 2.

**Fig. 2 Fig2:**
[figure not shown]
Trial flow chart. IVIG intravenous immunoglobulin

Antibody-positive patients will be given the patient information sheet and members of the research team will clarify any information which may preclude recruitment. Informed consent will be obtained by a researcher or a doctor at the screening visit before trial-specific assessments.

Participants lacking the capacity to make a decision to take part in the study will be approached to be enrolled in the study under the conditions and principles listed in the Medicines for Human Use (Clinical Trials) Regulations [26].

A Personal Legal Representative (PeLR) close to that incapacitated patient, aware of his/her wishes and independent of the research, should be approached first to provide written consent. If it is not possible to approach a personal legal representative or there is no one sufficiently close to the potential participant who is willing or able to take on the role, then an independent clinician will be nominated to act as Professional Legal Representative (PrLR) to fulfil this role. The PrLR in the SINAPPS2 trial is defined as a person who is not connected with the conduct of the trial, specifically not the Sponsor of the trial, nor a person employed or engaged by acting under the arrangements with the Sponsor, and who undertakes activities connected with the management of the trial, not an investigator of the trial and not a health care professional who is a member of the investigators’ team for the purposes of the trial.

Participants who regain capacity will be informed of the clinical trial and consent to continue will be sought at that time as per the usual consenting process.

If a participant consents to the trial but later becomes incapacitated, the original consent given remains valid after the loss of capacity, providing that the trial has not significantly altered.

### Screening, baseline, treatment and follow-up

#### Outline

Screening assessments and procedures, summarised in Fig. 1, will only be conducted after a participant has signed the consent form. Participants will be randomised after confirmation of their eligibility, and before the baseline visit. The eligibility must be confirmed within a maximum of 2 months from the informed consent. There is no other time limit for randomisation. The baseline visit will be scheduled a maximum of 4 weeks after confirmation of eligibility and a maximum of 7 days before IVIG/placebo treatment. Rituximab first infusion will follow after 4–5 weeks and rituximab second infusion 2–3 weeks later. All trial participants will be required to attend follow-up clinical visits at 3, 6, 9 and 12 months, which will be an end of study visit. Participants may need to be followed for longer and attend a clinical visit at month 15 and 18 if the primary outcome data need to be obtained beyond month 12. In addition, a monthly follow-up brief telephone or visit assessment will be administered by researchers. Anonymised data will be transferred in Case Report Forms (CRFs) by the trial researchers and clinicians. All CRFs will be completed in the manner, and within the timelines, detailed in the CRF-completion guidelines and sent to the trial coordinator at the Cambridge Clinical Trials Unit (CCTU). The CRFs will be accessible to trial coordinators, data managers, the investigators, clinical trial monitors, auditors and inspectors as required. All trial data will be entered and stored in a MACRO database. A trial-specific data management plan will describe in detail the data management processes.Screening visit and Assessments (Visit 1)

The screening visit and assessments will usually be performed at the SINAPPS2 site local clinical research facility, but may also be performed at outpatient clinics. Informed signed consent will be obtained and this will be followed by screening assessments to establish eligibility. These will include physician review, physical examination, height and weight assessments, pregnancy test (urine sample) if appropriate, collection of demographic data and disease history, screening blood tests, monitoring blood tests, anti-neuronal membrane antibody assays, blood sample for future research, assessment of PANSS items P1, P2, P3, N1, N4, N6, G5 and G9, and concomitant medications.2.Baseline visit and assessments (Visit 2 (day 0, maximum 7 days before IVIG/placebo treatment))

The baseline visit will follow confirmation of a participant’s eligibility and randomisation. It will be arranged a maximum of 4 weeks after confirmation of eligibility. Participants will be reviewed by a physician for the period between screening and baseline dates. Clinical assessment (PANSS), assessment of adverse events and concomitant medication will be administered by a researcher.3.IVIG or placebo treatment (Visit 3 (days 1–4))

The first treatment will follow the baseline visit (0–7 days after baseline) and will be given in an appropriate outpatient or inpatient setting, as determined by local practice and clinical need. Data on adverse events and concomitant medication will be obtained.4.Rituximab or placebo 1 treatment (Visit 4 (day 28, + 7 days)

Rituximab or placebo first treatment will be given in an appropriate setting, as determined by local practice and clinical need. Anti-neuronal membrane antibody assays and a pregnancy test (a maximum of 7 days before the first dose of rituximab/placebo) will be taken and data on adverse events and concomitant medications will be recorded.5.Rituximab or placebo 2 treatment (Visit 5 (day 42, + 7 days)

Rituximab or placebo second treatment will take place 14 (+ 7) days after the rituximab first treatment and data on adverse events and concomitant medications will be collected.6.Follow-up clinical visits (months 3, 6 and 9 (12 and 15), ± 7 days)

Each study participant will be followed for 12 months from the day of first treatment (IVIG/placebo). There will be an additional maximum 6 months of follow-up, if required, to assess the primary outcome if the participant enters clinical remission between months 7 and 12 (to include follow-up for a further 6 months from the point of entering clinical remission). Participants will be assessed every 3 months (at months 3, 6 and 9 (and months 12 and 15 if required for participants requiring longer follow-up) ± 7 days). At follow-up clinical visits there will be a physician review, a physical examination, assessment of severity of symptoms (PANSS), adverse events and concomitant medications. In addition, monitoring blood tests and anti-neuronal membrane antibody assays will be performed at month 6 (and month 12).7.End of trial visit (month 12 (or 15 or 18) ± 7 days).

Participation will end 12 months after the first day of treatment, or at 15 or 18 months if required. Assessments will include a physician review, physical examination, weight, monitoring blood tests, anti-neuronal membrane antibody assays, assessment of PANSS, adverse events and concomitant medications.

Participants will return to a normal standard of care after participation in the trial, which is likely to be a local psychiatry review, with a neurologist’s input and review if antibodies and symptoms return.8.Monthly telephone or visit follow-up assessments will be conducted by researchers to assess the primary outcome, adverse events and concomitant medication at months 1, 2, 4, 5, 7, 8, 10 and 11 (months 13, 14, 16 and 17 if required) ± 3 days. A month-one follow-up assessment will be conducted at the first rituximab treatment visit on day 28 (+ 7).

### Emergency unblinding

In the event of a clinical adverse event, where knowledge of the treatment allocation will alter management, the treating physician may unblind the patient using the web-based randomisation system (through a procedure documented in the trial manual/randomisation system manual). It is the responsibility of the treating physician to promptly document and explain any unblinding to the Sponsor.

### Withdrawal

Patients who have withdrawn from the allocated treatment will remain in the trial and be followed up as set out in the protocol, unless they withdraw their consent for this trial. Any data and samples collected up until that point of consent withdrawal will continue to be used in the trial. However, no further information will be collected or tests performed. Participants who withdraw between randomisation and treatment will be replaced.

In addition, participants must be withdrawn from their allocated treatment arm if they develop severe encephalopathy (e.g. typical of NMDAR encephalitis or LGI1-antibody encephalopathy), which would necessitate withdrawal to facilitate best standard of care of management for these conditions [7]; the participant develops severe reactions to the Investigational Medicinal Products (IMP) (e.g. anaphylaxis to first rituximab infusion, aseptic meningitis to first dose of IVIG); or a female participant becomes pregnant or will no longer use contraception.

### Trial restrictions

Women of childbearing potential are required to use adequate contraception for the duration of the trial and for 12 months after the last treatment. Men are required to use adequate contraception for the entire duration of the trial and for 90 days after the completion of the last treatment. Male participants should refrain from donating sperm for the duration of the trial and for 12 months thereafter.

### Sample size

To estimate the control rate for the primary outcome efficacy measure, we have re-analysed the raw data of the National EDEN study [27]. This study consisted of 1000 patients with psychosis (antibody associations not known); 19% of those, who were symptomatic at entry, experienced sustained remission as per the Andreasen et al. criteria [21] on standard antipsychotic therapy at 1 year. The 50% remission rate on immunotherapy that we have selected is a conservative estimate; in anti-NMDAR encephalopathy, remission may be as high as 85% at 1 year following IVIG and rituximab [7]. We agreed on 50% as a clinically meaningful and important remission rate that from a patient perspective would make participation in the trial acceptable. The Trial Steering Committee (TSC) and statistician will analyse recruitment and dropout rates at months 12 and 24 of the trial, and consider altering the recruitment strategy. We have chosen a sample size to target a time-to-remission hazard ratio of 0.322 with a one-sided type I error rate of 5% and a power of 80%, standard for a stage II clinical trial. This target hazard ratio comes from assuming a 1-year remission probability of 0.2 in the control arm and 0.5 in the experimental arm and assuming the time-to-remission distribution is exponential with proportional hazards. With all participants followed up for 1 year, a sample size of 56 participants equally randomised between the control and experimental arms is required. The sample size was calculated using NCSS PASS v14. We intend to recruit about 80 participants, allowing dropout of 12 participants per arm. This level of dropout is a cautious estimate because, although a high dropout is often seen in drug trials in psychosis, we are not requiring continued compliance with medication regimes after the infusions of IVIG and rituximab.

### Statistical analysis methods

The final analysis will use a Cox proportional hazards model with fixed effects for minimisation covariates. The primary analysis will be per protocol rather than intention to treat, although both will be done. Secondary and exploratory outcomes will be analysed with Cox models (time to any remission), logistic regression models (relapse rate, proportion of participants with serious adverse events) and Poisson models (number of adverse events). The per-protocol population is defined as all participants who have received all protocol-defined IMPs, and have no major protocol violation as defined prior to analysis. A full detailed analysis plan will be prepared by a statistician who is independent from the study.

Data on trial progress such as recruitment and participant dropout at months 12, 24 and 36 of the trial (after activation of the first site) and quality of data will be reported to both the Trial Steering Committee and the Data Monitoring Committee (DMC). The Trial Steering Committee will consider opening additional sites and/or modifying eligibility criteria if recruitment rates are below those expected. There will be no interim analyses of efficacy.

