### Participants

#### Inclusion criteria

Age 18–70 years.Acute psychosis symptoms for at least 2 weeks but not longer than 24 months in the current episode. Acute psychosis is defined as rating 4 or more for at least one of the following Positive and Negative Syndrome Scale (PANSS) [18] items: P1, delusions; P2, conceptual disorganisation; P3, hallucinatory behaviour; N1, blunted affect; N4, social withdrawal; N6, lack of spontaneity; G5, mannerisms/posturing; and G9, unusual thought content. This may be either a first episode or relapse after remission. Remission is defined as having mild or absent symptoms of psychosis for at least 6 months.Serum or cerebrospinal fluid (CSF) anti-neuronal membrane antibodies at pathological levels (including NMDAR, LGI1 and others, as determined by the Trial Steering Committee).Given informed consent by a patient or their legal representative.

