### Randomisation

An Internet-based system provided by Sealed Envelope will be used to randomise participants and allocate treatment to individual patients [19]. Eligible patients will be randomly assigned 1:1 to either the IVIG/rituximab group or the placebo group before the baseline assessment. Each group will contain approximately 40 participants. The randomisation will be performed using the minimisation technique of Pocock and Simon [20], using NMDAR (yes vs no), LGI1 (yes vs no), GABA-A (yes vs no), duration of psychotic illness (less than 12 weeks vs 12 weeks and longer) and current smoking status (currently smoking vs currently not smoking) as dichotomous minimisation factors.

Notification of treatment allocation will be forwarded to the central trial coordinator, local investigator and local pharmacy by email upon randomisation.

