### Primary outcome

The primary outcome is the time to start of symptomatic recovery. Symptomatic recovery is defined as symptomatic remission sustained for at least 6 months [21]. Symptomatic remission is defined as a score of 3 or less on each of the following PANSS [18] items: P1, P2, P3, N1, N4, N6, G5 and G9.

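### Entry severity sets the distance to the remission endpoint on the same eight PANSS items, but it is neither a minimisation factor nor a stated Cox covariate: a missed gain in precision

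*Protocol article*

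**What the plan says.** All references are to the protocol article.

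- **Inclusion criteria:** "Acute psychosis is defined as rating 4 or more for at least one of the following" eight PANSS items (P1, P2, P3, N1, N4, N6, G5, G9). There is no upper limit on severity.
- **Primary outcome:** "Symptomatic remission is defined as a score of 3 or less on each of the following PANSS [18] items", and the items listed are the same eight. The primary event also requires this state to last at least 6 months.
- **Primary outcome measure:** items are scored from 1 to 7, so 3 and 4 are neighbouring scores.
- **Randomisation:** minimisation is done "using NMDAR (yes vs no), LGI1 (yes vs no), GABA-A (yes vs no), duration of psychotic illness" (cut at 12 weeks) and "current smoking status (currently smoking vs currently not smoking) as dichotomous minimisation factors". No severity measure is listed.
- **Statistical analysis methods:** "The final analysis will use a Cox proportional hazards model with fixed effects for minimisation covariates". The same section refers to a separate detailed analysis plan.
- **Screening, baseline, treatment and follow-up:** the eight items are rated at the screening visit. Randomisation follows confirmation of eligibility and precedes the baseline visit, where PANSS is rated again before treatment.

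**The concern.** The two thresholds sit side by side on the same items. One participant may enter with a single item at 4, one point on one item from the remission score. Another may enter with several items at 6 or 7. Both contribute equally to the treatment comparison, and neither the allocation nor the stated model takes account of the difference.

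With few events, two things are at stake. A chance difference between the arms in entry severity goes uncorrected in the estimated hazard ratio. And if severity predicts remission, the analysis leaves unused a variable that is already collected and could sharpen the test.

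**Working it through.** **1. The plan's own figure.** From the Sample size section: 1-year remission 0.2 versus 0.5, exponential times, one-sided 5%, 80% power, 1:1 allocation, 1 year of follow-up.

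- Hazard ratio = ln(0.8)/ln(0.5) = 0.322, as stated.
- Schoenfeld events = 4 × (1.645 + 0.842)² / (ln 0.322)² = 19.25, rounded up to 20.
- Mean event probability = (0.2 + 0.5)/2 = 0.35. Participants = 19.25/0.35 = 55.0, or 20/0.35 = 57.1.
- The stated 56 reproduces. Expected events at 56 are 56 × 0.35 = 19.6, and Schoenfeld power is 80.6%.

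**2. Is 0.322 already averaged over severity?** Yes. It is derived from whole-arm remission probabilities, which mix mild and severe participants. In simulations with the marginal probabilities held at 0.2 and 0.5 and no other covariates, the hazard ratio conditional on severity was 0.309, 0.285 and 0.237 for a 1.5-, 2- and 3-fold hazard per SD. The median unadjusted estimate stayed at 0.32, 0.32 and 0.31. Leaving severity out therefore does not push the trial below its planned effect.

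**3. Chance imbalance.** With 28 per arm and no balancing on severity, the SD of the between-arm difference in mean severity is √(2/28) = 0.267 SD units. P(|difference| > 0.5 SD) = 2 × [1 − Φ(0.5/0.267)] = 0.061, about 6%. To a first approximation, a 0.5 SD imbalance multiplies the unadjusted hazard ratio by k^−0.5 or its inverse, where k is the fold change in hazard per SD: 0.82 for k = 1.5, 0.71 for k = 2, 0.63 for k = 2.5.

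**4. Power with and without a severity term.** Cox simulation with 56 participants, one-sided 5%, marginal remission 0.2 versus 0.5, five binary covariates already in the model, 1,500 runs per setting. The fold change is assumed.

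| Hazard change per SD | Power without | Power with | Gain (points) |
|---|---|---|---|
| 1 (not prognostic) | 76% | 76% | 0 |
| 1.5-fold | 78% | 80% | 2 |
| 2-fold | 78% | 82% | 4 |
| 2.5-fold | 79% | 86% | 7 |

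Null rejection was 4–6% without severity and 6–7% with it. Two further runs of the same design (2,000 and 3,000 runs per setting) gave gains of 1–2, 5 and 7–8 points for the three prognostic settings; the highest null rejection with severity was 7.8%, against 6.6% without it in that setting. A simpler model, with treatment and severity only, lost about 1 point of power when severity was not prognostic and kept null rejection at about 3.5–5%. The slight excess therefore appears only in the model with six covariates.

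**5. Which score measures the distance?** Remission requires every item at 3 or less, so the plain sum can rank participants wrongly.

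| Profile | Sum of items | Points above 3 |
|---|---|---|
| One item at 4, seven at 3 | 4 + 21 = 25 | 1 |
| One item at 7, seven at 1 | 7 + 7 = 14 | 4 |

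The first is closer to remission but has the larger sum. Total points above 3 orders the two correctly.

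**6. Age of the screening score.** Eligibility may take up to 2 months from consent, baseline up to 4 more weeks, and treatment up to 7 more days: about three months in all.

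**The case against.** A Cox model adjusted for the minimisation factors is the standard companion to this allocation method, and randomisation keeps the test valid without severity. The article does not say that these are the only covariates, and the separate analysis plan could add one. All of this stands. The point is therefore about a choice the article does state, for a variable tied to the endpoint by definition, and not about a contradiction.

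Several stronger readings are tempting, and the documents do not support them.

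- **That omission costs planned power.** Step 2 shows the target hazard ratio is already marginal, and unadjusted power in step 4 does not fall as severity becomes more prognostic.
- **That chance imbalance makes the result biased or the error rate wrong.** The 6% figure applies to any unbalanced covariate, and its effect is already within the nominal error rate. Any selection introduced by the per-protocol population is a separate question.
- **That the mildest participants will remit whatever they receive.** The Background reports that nine of 18 patients with NMDAR antibodies resolved or responded to antipsychotics, but gives no severity for them.
- **That a participant with one item at 4 is one point from the primary event.** The primary event also needs six months of sustained remission.

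It is also fair to object that the gain rests wholly on an assumed prognostic strength, that part of it reflects slightly anti-conservative testing with six covariates, and that the simulations treat severity as perfectly measured and log-linear, so no actual score is guaranteed the tabulated gain. Illness duration may already carry some of the same prognostic information.

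**Conclusion.** The point holds as a recommendation on efficiency. The entry and remission definitions make severity the required distance to the endpoint, and the stated allocation and model both leave it out although it is measured before randomisation. With 19.6 expected events, adding it would raise power by about 2 to 7 points if one SD changes the remission hazard 1.5- to 2.5-fold, and would gain nothing or lose about 1 point if severity is not prognostic. It would also adjust for chance imbalance in severity. The sample size of 56 is not in error, and the planned test is valid without the term. The size of the benefit depends on a prognostic strength that the documents do not give.

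**What to change.** Keep the minimisation factors and pre-specify, before unblinding, one continuous severity term in the primary Cox model and in the time-to-remission model. Use a score that measures distance to the threshold, such as the total points above 3 across the eight items, rated at screening. It precedes randomisation and needs no new data. Because screening may precede treatment by about three months, repeat the analysis with the pre-treatment baseline PANSS as a sensitivity analysis.

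The change is a line or two in the analysis plan. The costs should be stated there:

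- Parameters rise from six (treatment and five factors) to seven, so events per parameter fall from 19.6/6 = 3.3 to 19.6/7 = 2.8.
- Null rejection may be about 1 to 2 points higher, at roughly 6–7% against the nominal 5%.
- The reported hazard ratio becomes conditional on severity, so it is not directly comparable with the planning value of 0.322.

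### The primary analysis of this superiority trial is per protocol, so participants whom the protocol itself takes off treatment drop out of the main comparison although they are still followed up

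*Protocol article*

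**What the plan says.** The Background section gives the aim as superiority of IVIG plus rituximab over conventional psychiatric care. Statistical analysis methods then fixes the analysis set: "The primary analysis will be per protocol rather than intention to treat, although both will be done". Membership depends on completing treatment: "The per-protocol population is defined as all participants who have received all protocol-defined IMPs", with the further condition of no major violation.

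The Withdrawal section makes some incomplete treatment compulsory: "participants must be withdrawn from their allocated treatment arm if they develop severe encephalopathy". The same applies to severe reactions to the trial drugs, with the examples "anaphylaxis to first rituximab infusion, aseptic meningitis to first dose of IVIG", and to pregnancy or stopping contraception. For encephalopathy the stated purpose is "withdrawal to facilitate best standard of care of management for these conditions". Unless consent is withdrawn, these people are not lost: "Patients who have withdrawn from the allocated treatment will remain in the trial and be followed up as set out in the protocol".

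The visit schedule puts the first rituximab or placebo infusion at day 28 (+7). For the last one: "Rituximab or placebo second treatment will take place 14 (+ 7) days after the rituximab first treatment".

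**The concern.** Anyone taken off treatment before the last infusion has not received every trial drug and so leaves the primary analysis by definition. Nothing makes these departures comparable between arms. The reactions given as examples are to IVIG and rituximab, whereas the Placebo section specifies 1% albumin and saline. Encephalopathy belongs to the course of the disease under study and may be more or less frequent according to treatment.

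The bias could run either way:

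- Removing active participants who react favours active treatment if they were unlikely to recover, works against it if they would have recovered, and does nothing if reaction and recovery are unrelated.
- Removing placebo participants with encephalopathy hides benefit if they would not have recovered, and does the opposite if they recover on the care they are then given.

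If the two planned analyses disagree, the one designated primary decides the trial, and here that is the one randomisation does not protect.

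**Working it through.** **The plan's own figure.** Inputs from the Sample size section: 1-year remission 0.2 v 0.5, exponential times, one-sided 5%, power 80%, 1:1 allocation.

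- Hazard ratio = ln(1 − 0.2) / ln(1 − 0.5) = 0.322.
- Schoenfeld events = 4 × (1.645 + 0.842)² / (ln 0.322)² = 19.26.
- Mean event probability = (0.2 + 0.5)/2 = 0.35, so N = 19.26/0.35 = 55.02, rounded up to 56 in equal arms.
- Dropout of 24 in 80 is 30%, and 56/(1 − 0.30) = 80.

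The sample size reproduces. The choice of analysis set is the issue.

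**The window for exclusion.** The latest last infusion is 28 + 7 + 14 + 7 = day 56, about 8 weeks from first treatment.

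**Effect of removing people on the null.** With 20% recovery in both arms and 40 per arm, if k active participants who would not recover are removed, the apparent active-arm rate is 0.2 × 40/(40 − k). For k = 1, 2, 4 that is 20.5%, 21.1% and 22.2%, equivalent to recovery hazard ratios (active over placebo) of 1.03, 1.06 and 1.13 where the truth is 1.

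**Simulation.** Log-rank test, exponential times, 1 year of follow-up, 40 randomised per arm, no other dropout, one-sided 5%, 40,000 runs per cell. The values of k are assumptions. Counts should be small, because Exclusion criteria rules out current acute encephalopathy and known hypersensitivity, and the window is short.

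Type I error, no true effect, k active participants removed:

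| Those removed | k = 1 | k = 2 | k = 4 |
|---|---|---|---|
| All non-recoverers | 5.7% | 6.3% | 8.4% |
| Unrelated to recovery | 5.1% | 4.9% | 5.2% |
| All recoverers | 3.4% | 2.3% | 0.8% |

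Power, true 20% v 50% (90% with nobody affected):

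| Scenario | k = 2 | k = 4 |
|---|---|---|
| Per protocol, k placebo non-recoverers removed | 86% | 82% |
| Per protocol, k placebo removed, unrelated to recovery | 89% | 88% |
| Intention to treat, k placebo cases, none recover | 92% | 93% |
| Intention to treat, k placebo cases, 85% recover after rescue | 82% | 71% |
| Intention to treat, k active miss infusions and recover at 20% | 87% | 84% |
| Per protocol, those k active excluded | 89% | 88% |

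The 85% is borrowed from the Sample size section, which says of anti-NMDAR encephalopathy that "remission may be as high as 85% at 1 year following IVIG and rituximab". Whether rescue care in this trial would be that treatment, or work that well, is an assumption.

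**The case against.** The choice is open and deliberate. This is a phase IIa trial, and the Limitations section says that it addresses efficacy and leaves effectiveness for later. Intention to treat will be reported alongside, so no participant's data disappear. No rates are given, few exclusions are likely, and the 8.4% needs four exclusions, all on active treatment and all non-recoverers. Intention to treat has a real weakness of its own: placebo patients with encephalopathy may be rescued with the test treatment, which dilutes the contrast.

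The 40-per-arm simulations also ignore the planned dropout. At 28 per arm, baseline power is about 78–79%. Intention-to-treat power with two or four rescued placebo cases is about 63% or 47%, against about 77% or 74–75% if those cases are excluded unrelated to recovery. The worst-case per-protocol error with two or four active exclusions also rises, to about 7% or 10%. Finally, an all-randomised set needs more definition than the article gives, because the Withdrawal section replaces participants who leave between randomisation and treatment and stops data collection once consent is withdrawn.

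Much of this stands as a limit on size: the effect may be negligible, and the power cost of rescue could exceed the distortion removed. It does not answer the point itself. Wanting the effect of full treatment does not make those who completed it comparable between arms, and the article states no adjustment that would. Dilution by rescue costs power but does not raise the false-positive rate, whereas selective exclusion can. Participants who withdraw consent can be censored in the Cox model.

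**Conclusion.** The concern holds. The article explicitly makes a completers' analysis primary in a superiority trial, and its own withdrawal rules generate exclusions that cannot be presumed balanced or unrelated to recovery. This is a stated choice, not a detail left to the analysis plan, and a plan that follows the protocol would inherit it.

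No size or direction can be claimed. Under the assumed one to four exclusions from the active arm, the nominal 5% error lies anywhere between 0.8% and 8.4%, and stays near 5% if exclusion has nothing to do with recovery. These figures rest on 40 per arm, exponential times and all exclusions falling in one arm. The reported intention-to-treat analysis softens the problem but does not remove it while it remains secondary. The change should be made because it is cheap and restores a comparison protected by randomisation.

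**What to change.** In Statistical analysis methods, reverse the two roles. The primary analysis becomes intention to treat: all randomised participants, analysed as allocated, using the follow-up that continues after treatment withdrawal. The per-protocol analysis becomes the sensitivity analysis. State that participants replaced before treatment remain in the all-randomised set and that those who withdraw consent are censored at that point. Report the number excluded from the per-protocol set by arm and by reason for withdrawal.

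The cost is a short wording change. It needs no extra visits, data or analyses, and the calculated 56 (80 recruited) is unchanged. The power losses shown in the tables are the downside. The per-protocol result, with the exclusions listed by reason, will show readers whether rescue treatment on placebo has diluted the primary estimate.
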